### ***4.2.3 Discontinuation of Subjects from Treatment***

Subjects will be treated with combination therapy until the completion of 4 cycles of therapy, irPD, subject refusal or excessive toxicity.

Subjects MUST discontinue investigational product (and non investigational product at the discretion of the investigator) (investigational or non investigational treatment) for any of the following reasons:

- Withdrawal of informed consent (subject's decision to withdraw for any reason),
- DLT,
- Any clinical adverse event (AE), laboratory abnormality or intercurrent illness that, in the opinion of the investigator, indicates that continued participation in the study is not in the best interest of the subject,

NOTE: In case of excessive toxicity, if the observed AE leading to treatment discontinuation is unequivocally attributable to only 1 of the 2 investigational drugs, patient might still receive the other drug at the investigator discretion

- Pregnancy (see Section 7.7),

- Termination of the study by NIBIT,
- Loss of ability to freely provide consent through imprisonment or involuntarily incarceration for treatment of either a psychiatric or physical (eg, infectious disease) illness.

All subjects who discontinue should comply with protocol specified follow-up procedures as outlined in Section 6. The only exception to this requirement is when a subject withdraws consent for ALL study procedures or loses the ability to consent freely (i.e, is imprisoned or involuntarily incarcerated for the treatment of either a psychiatric or physical illness).

If a subject was withdrawn before completing the study, the reason for withdrawal must be entered on the appropriate case report form (CRF) page.

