## **5.3 Dose-limiting Toxicity**

DLT is defined as any of the following events occurring during the first treatment cycle and clearly related to study treatment: grade 4 neutropenia (absolute granulocyte count < 0.5 x 10^9/L, ≥ 5 days), febrile neutropenia grade ≥ 3 (absolute granulocyte count < 1.0 x 10^9/L and fever ≥ 38.5° C), platelet count < 25.000/L or thrombocytopenic bleeding, AST or ALT grade ≥ 3 for 7 days, any grade 3 or 4 non-hematologic toxicity (excluding alopecia, non pre-medicated nausea and vomiting), grade 3 or 4 clinically

significant nausea, vomiting, or diarrhoea in the presence of maximal supportive care, a required interruption of treatment > 2 weeks due to toxicity. If the toxicity fails to resolve to  $\leq$  grade 2 with 14 days off treatment, the patient will be removed from the study.

Inability to initiate Cycle 2 within 2 weeks of scheduled treatment due to slow recovery from study drug-induced toxicities and failure to meet re-treatment criteria.

The DLT observation period is defined as the first 3 weeks of treatment, i.e., from Day 1 to Day 21 of Cycle 1. Once the MTD is reached in each group, the safety data will be analysed.

Note: All AEs (including those occurring after the end of the DLT observation period) will be considered for decision-making by the SMC.

**Tolerability** will be defined as the ability to continue treatment for at least 2 cycles in a row without development of DLTs.

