### ***5.3.1 Dose Modifications***

During dose escalation, the dose of SGI-110 to be administered is determined by the dose level and the subject's body weight at consent. Thereafter, it will be determined by the MTD and the subject's body weight. Once a dose of SGI-110 is established, it should be maintained unless the subject's body weight decreases by 10% or a safety issue requires dose reduction. If a myelosuppressive DLT occurs, the patient may resume at the next lower dose level of SGI-110 after recovery of counts.

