### ***Dose Delay Criteria for SGI-110***

The Investigator should try to the best of his/her ability to assess whether an adverse event is related to SGI-110 treatment. If the adverse event is judged to be related to SGI-110 dosing delay may be recommended according to the following guidelines:

In case of drug-related Grade 3 or 4 non-hematological toxicity, or Grade 4 hematological toxicity, dosing should be delayed until the subject recovers to levels consistent with the eligibility criteria if specified, or the subject's baseline status otherwise, and dosing should be resumed at the same dose. In case of asymptomatic uncomplicated Grade 4 hematological toxicity that lasts no more than one week, a subject may be redosed at the same dose level following recovery during the week prior to the next dose of ipilimumab as specified above per investigator's judgment.

Dose delay criteria apply for all drug-related adverse events (regardless of whether or not the event is attributed to SGI-110). All study drugs must be delayed until treatment can resume.

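### Section 4.2.3 requires SGI-110 to stop after any DLT, while section 5.3.1 lets it resume one level lower after a myelosuppressive DLT; the same-dose delay rule also fails to exclude DLTs

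*Combined protocol and SAP*

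**What the plan says.** **Definition.** Section 5.3 states: "DLT is defined as any of the following events occurring during the first treatment cycle and clearly related to study treatment: grade 4 neutropenia". The duration threshold for that item is 5 days or more. The same section removes a patient whose toxicity has not come down to grade 2 or less: "with 14 days off treatment, the patient will be removed from the study".

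**Stop.** Section 4.2.3 opens its list with "Subjects MUST discontinue investigational product", and one bullet is DLT with no qualifier. Section 5.1.1 counts both SGI-110 and ipilimumab as investigational products. The note in 4.2.3 covers excessive toxicity clearly caused by one drug only, and says the "patient might still receive the other drug at the investigator discretion". It gives no route back to the drug that caused the event.

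**Resume one level lower.** Section 5.3.1: "If a myelosuppressive DLT occurs, the patient may resume at the next lower dose level of SGI-110 after recovery of counts".

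**Resume at the same dose.** The SGI-110 dose delay criteria, a sub-heading within 5.3.1, cover drug-related grade 3 or 4 non-hematological and grade 4 hematological toxicity. After recovery to eligibility levels or baseline, "dosing should be resumed at the same dose". A further sentence deals with short events: "In case of asymptomatic uncomplicated Grade 4 hematological toxicity that lasts no more than one week". Such a patient can be treated again at an unchanged level once recovered, if the investigator so judges. DLTs are not excluded.

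None of these texts refers to another or states which takes precedence.

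**The concern.** Myelosuppression is the expected toxicity of SGI-110, and section 1.3.5.1 says that recovery from it will probably determine the safe dose on a 21-day cycle, for which it says little data exist. A recovered myelosuppressive DLT is therefore a foreseeable case. An investigator who follows 5.3.1 and re-treats at the lower level departs from a mandatory instruction in 4.2.3. An investigator who follows 4.2.3 withholds treatment that 5.3.1 allows and that section 4.1.1 (End of Treatment) encourages patients to complete.

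What is at stake is whether, and at what dose, a patient is re-exposed to the drug that caused the DLT. Section 4.1.3 sends potential DLTs to the Safety Monitoring Committee by the end of the business day. The decisions it lists for the committee concern DLT designation, dose and schedule, enrolment and the MTD. Re-treatment of an individual patient is not among them.

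**Working it through.** The plan gives no figure of its own on this point. The check applies each rule to one case and then works out the planned dose under each.

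**1. The case.** Drug-related grade 4 neutropenia in Cycle 1, lasting 6 days, asymptomatic, uncomplicated and recovered.

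- Section 5.3: 6 days is at least 5, so it is a DLT.
- Section 4.2.3: a DLT, so SGI-110 must stop.
- Section 5.3.1: a myelosuppressive DLT with recovered counts, so SGI-110 may resume one level lower.
- Delay criteria, general sentence: grade 4 hematological toxicity, so after recovery the same dose is resumed. There is no limit on duration.
- Delay criteria, one-week sentence: 6 days is no more than 7, so same-level redosing is allowed.

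**2. Overlap in duration.** DLT requires d ≥ 5; the one-week sentence requires d ≤ 7. Both hold for 5 ≤ d ≤ 7 days. Recovered events longer than 7 days are still reached by the general sentence, subject to the 14-day removal rule in 5.3.

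**3. Planned SGI-110 exposure.** Inputs: dose levels of 15, 30, 45 and 60 mg/m2/day, five doses per cycle and four cycles (sections 5.2.1 and 5.2.2). Assumptions: all five Cycle 1 doses precede the event, and every later cycle allowed by the rule is given.

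Per cycle = daily dose × 5 = 75, 150, 225 and 300 mg/m2. Cycles 2 to 4 = 3 × the per-cycle dose at the level given.

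| DLT at level | Stop (4.2.3) | One level lower (5.3.1), maximum | Same dose (delay criteria) | Same ÷ lower |
|---|---|---|---|---|
| 0 (30) | 0 | 3 × 75 = 225 | 3 × 150 = 450 | 2.0 |
| +1 (45) | 0 | 3 × 150 = 450 | 3 × 225 = 675 | 1.5 |
| +2 (60) | 0 | 3 × 225 = 675 | 3 × 300 = 900 | 1.33 |
| -1 (15) | 0 | no level defined | 3 × 75 = 225 | n/a |

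Adding Cycle 1 gives whole-course totals (stop / lower / same) of 150 / 375 / 600 at Level 0, 225 / 675 / 900 at Level +1 and 300 / 975 / 1200 mg/m2 at Level +2. The one-level-lower column is a maximum because resumption is optional.

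**4. Two gaps that a repair must cover.** At Level -1 there is no next lower level. And because 5.1.1 makes ipilimumab investigational, the 4.2.3 bullet also reaches ipilimumab after a non-hematological DLT. Yet the ipilimumab delay criteria let treatment resume when an endocrinopathy is controlled on physiologic hormone replacement, and 5.3.2 exempts most grade 3 laboratory abnormalities from discontinuation.

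**The case against.** **Section 5.3.1 can be reconciled with the delay criteria.** The sentence before the DLT sentence keeps an established dose unless weight loss or a safety issue calls for a reduction. The delay criteria sit under the same section, are introduced as guidelines, and keep work of their own: later-cycle toxicity and shorter Cycle 1 neutropenia. On that reading the same dose is the default and a myelosuppressive DLT is the specific exception. This largely stands. A reader might infer three instructions of equal weight with nothing to choose between them; the documents do not support that. What remains is that the same-dose sentences do not exclude DLTs, and that the one-week limit runs past the 5-day DLT threshold.

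**Sections 4.2.3 and 5.3.1 can be reconciled.** Section 5.3.1 only permits resumption, so stopping breaches neither section. Section 4.2.3 says discontinue, whereas other sections say permanently when no return is meant. The 14-day removal rule in 5.3 also suggests that recovered patients were meant to stay on treatment. This shows which rule was probably intended and makes the 4.2.3 bullet the outlier. It does not remove the conflict: that list also holds pregnancy and withdrawal of consent, which are not temporary pauses, and its only relief is for the other drug.

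**The consequence is narrow.** Only patients whose DLT recovers are affected, and re-treatment under the delay criteria already requires recovery to eligibility levels (ANC at least 2000/µL, platelets at least 100 × 10^3/µL) or baseline. This stands and limits the weight of the point.

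**Conclusion.** The concern holds as an internal inconsistency that should be fixed. The main conflict is the unqualified DLT bullet in 4.2.3 against the permission in 5.3.1 to resume one level lower. The secondary conflict is the same-dose rule, which does not exclude DLTs, although 5.3.1 is best read as governing.

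Depending on the text followed, planned exposure in Cycles 2 to 4 runs from 0 to 450, 675 or 900 mg/m2 after a DLT at Level 0, +1 or +2. The same-dose total is 2.0, 1.5 or 1.33 times the reduced one. This assumes that all later cycles are given. The documents state no DLT rate, so a reader should not take these totals as a measure of how often patients would be affected or harmed.

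A reader might also infer that the escalation decision or the MTD is compromised. The documents do not support that: the event is a DLT under 5.3 whatever happens afterwards, so the DLT count and the MTD rule are unchanged. Section 5.3 does let the Safety Monitoring Committee weigh later adverse events, and the re-treatment dose bears on those, but this does not alter the formal rule.

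**What to change.** Three wording edits:

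- **Section 4.2.3, DLT bullet:** *DLT, except a myelosuppressive DLT managed under 5.3.1 and, for ipilimumab, events for which 5.3.1 or 5.3.2 expressly allow treatment to resume or continue.*
- **SGI-110 dose delay criteria:** add *The same-dose rule does not apply to events that meet the DLT definition in 5.3.*
- **Section 5.3.1:** add *A patient with a DLT at Dose Level -1 discontinues SGI-110, as there is no lower level.*

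The first and second edits are not enough without the ipilimumab clause and the Level -1 sentence, because of the two gaps shown in the working. With all three, a recovered myelosuppressive DLT at Level 0 or above may resume one level lower, and the same DLT at Level -1 ends SGI-110. SGI-110 toxicity that is not a DLT returns to the same dose after recovery. The second edit also removes the same-dose instruction after a non-hematological DLT.

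The cost is a short amendment. It needs no new data and no change to the escalation rule. Reporting is also unchanged, since section 8.4.2 already tabulates omissions, reductions and delays.

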### ***Dose Delay Criteria for SGI-110***

The Investigator should try to the best of his/her ability to assess whether an adverse event is related to SGI-110 treatment. If the adverse event is judged to be related to SGI-110 dosing delay may be recommended according to the following guidelines:

In case of drug-related Grade 3 or 4 non-hematological toxicity, or Grade 4 hematological toxicity, dosing should be delayed until the subject recovers to levels consistent with the eligibility criteria if specified, or the subject's baseline status otherwise, and dosing should be resumed at the same dose. In case of asymptomatic uncomplicated Grade 4 hematological toxicity that lasts no more than one week, a subject may be redosed at the same dose level following recovery during the week prior to the next dose of ipilimumab as specified above per investigator's judgment.

Dose delay criteria apply for all drug-related adverse events (regardless of whether or not the event is attributed to SGI-110). All study drugs must be delayed until treatment can resume.

### ***Dose Delay Criteria for ipilimumab***

Because of the potential for clinically meaningful ipilimumab-related AEs requiring early recognition and prompt intervention, management algorithms have been developed for suspected AEs of selected categories.

Subjects may resume treatment with study drug when the drug-related AE(s) resolve to Grade  $\leq 1$  or baseline value, with the following exceptions:

- Subjects may resume treatment in the presence of Grade 2 fatigue,
- Subjects who have not experienced a Grade 3 drug-related skin AE may resume treatment in the presence of Grade 2 skin adverse event,
- Subjects with baseline Grade 1 AST/ALT or total bilirubin who require dose delays for reasons other than a 2-grade shift in AST/ALT or total bilirubin may resume treatment in the presence of Grade 2 AST/ALT OR total bilirubin,
- Subjects with combined Grade 2 AST/ALT AND total bilirubin values meeting discontinuation parameters should have treatment permanently discontinued,
- Drug-related pulmonary AEs, diarrhea, or colitis, must have resolved to baseline before treatment is resumed,
- Drug-related endocrinopathies adequately controlled with only physiologic hormone replacement may resume treatment.

Dose delay criteria apply for all drug-related adverse events (regardless of whether or not the event is attributed to ipilimumab). All study drugs must be delayed until treatment can resume.

If the criteria to resume treatment are met, the subject should restart treatment at the next scheduled timepoint per protocol. However, if the treatment is delayed past the next scheduled timepoint per protocol, the next scheduled timepoint will be delayed until dosing resumes. If treatment is delayed  $> 6$  weeks, the subject must be permanently discontinued from study therapy, except as specified below.

### ***5.3.2 Discontinuation Criteria***

#### ***Ipilimumab Permanent Discontinuation***

Treatment should be permanently discontinued for the following:

- Any Grade 2 drug-related uveitis or eye pain or blurred vision that does not respond to topical therapy and does not improve to Grade 1 severity within the re-treatment period OR requires systemic treatment
- Any Grade 3 non-skin, drug-related adverse event lasting > 7 days, including uveitis, pneumonitis, bronchospasm, diarrhea, colitis, neurologic adverse event, hypersensitivity reactions, and infusion reactions. Drug-related laboratory abnormalities are exceptions, as discussed below.
  - Grade 3 drug-related uveitis, pneumonitis, bronchospasm, diarrhea, colitis, neurologic adverse event, hypersensitivity reaction, or infusion reaction of any duration requires discontinuation
  - Grade 3 drug-related laboratory abnormalities do not require treatment discontinuation except those noted below
    - a. Grade 3 drug-related thrombocytopenia > 7 days or associated with bleeding requires discontinuation
    - b. Any drug-related liver function test (LFT) abnormality that meets the following criteria require discontinuation:
      - AST or ALT > 8 x ULN
      - Total bilirubin > 5 x ULN
      - Concurrent AST or ALT > 3 x ULN and total bilirubin > 2 x ULN
- Any Grade 4 drug-related adverse event or laboratory abnormality, except for the following events which do not require discontinuation:
  - Isolated Grade 4 amylase or lipase abnormalities that are not associated with symptoms or clinical manifestations of pancreatitis and decrease to < Grade 4 within 1 week of onset.
  - Isolated Grade 4 electrolyte imbalances/abnormalities that are not associated with clinical sequelae and are corrected with supplementation/appropriate management within 72 hours of their onset
- Any dosing interruption lasting > 6 weeks with the following exceptions:
  - Dosing interruptions to allow for prolonged steroid tapers to manage drug-related adverse events are allowed. Prior to re-initiating treatment in a subject with a dosing interruption lasting > 6 weeks, the Investigator must be consulted. Tumor assessments should continue as per protocol even if dosing is interrupted

- Dosing interruptions > 6 weeks that occur for non-drug-related reasons may be allowed if approved by the Investigator. Prior to re-initiating treatment in a subject with a dosing interruption lasting > 6 weeks, the Investigator must be consulted. Tumor assessments should continue as per protocol even if dosing is interrupted
- Any adverse event, laboratory abnormality, or intercurrent illness which, in the judgment of the Investigator, presents a substantial clinical risk to the subject with continued ipilimumab dosing

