**Investigational Product(s), Dose and Mode of Administration, Duration of Treatment with Investigational Product(s):**

SGI-110 is considered as Investigational Medicinal Product (IMP) and will be supplied by Astex and dispensed by Fondazione NIBIT /CRO. Ipilimumab will be utilized in the study according to the approved dose and schedule of administration for metastatic melanoma.

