#### ***5.1.1 Investigational Product***

An investigational product, also known as investigational medicinal product in some regions, is defined as follows:

A pharmaceutical form of an active substance or placebo being tested or used as a reference in a clinical study, including products already with a marketing authorization but used or assembled (formulated or packaged) in a way different from the authorized form, or used for an unauthorized indication, or when used to gain further information about the authorized form.

In this protocol, investigational products are SGI-110 and ipilimumab. Astex will supply SGI-110 to Fondazione NIBIT/CRO for this trial. Ipilimumab will be utilized in the study according to the approved dose and schedule of administration for metastatic melanoma.

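### Sections 5.3.2, 5.3.1 and 4.2.3 give different answers on whether ipilimumab continues after a Grade 4 drug-related cytopenia, and none is said to prevail

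*Combined protocol and SAP*

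**What the plan says.** **Section 5.3.2, ipilimumab permanent discontinuation.** One bullet reads "Any Grade 4 drug-related adverse event or laboratory abnormality, except for the following events which do not require discontinuation". The two exceptions begin "Isolated Grade 4 amylase or lipase abnormalities that are not associated with symptoms or clinical manifestations of pancreatitis" and "Isolated Grade 4 electrolyte imbalances/abnormalities that are not associated with clinical sequelae", and each carries a time limit. Neither concerns blood counts. Blood counts are nevertheless within the scope of the list, which includes among laboratory abnormalities "Grade 3 drug-related thrombocytopenia > 7 days or associated with bleeding requires discontinuation".

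**Section 5.3.1, dose delay for SGI-110.** After drug-related Grade 4 haematological toxicity, dosing waits for recovery and restarts at an unchanged dose. For asymptomatic, uncomplicated events of up to one week, "a subject may be redosed at the same dose level following recovery during the week prior to the next dose of ipilimumab". The delay criteria apply whichever drug is blamed, and they hold all study drugs until treatment can restart. The opening paragraph of 5.3.1 adds that, after a myelosuppressive DLT, SGI-110 may restart one level lower once counts have recovered.

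**Section 4.2.3.** The stop list begins "Subjects MUST discontinue investigational product (and non investigational product at the discretion of the investigator", and DLT is on it. A note then leaves it to the investigator whether the other drug continues when a toxicity is unequivocally due to one of the two investigational drugs.

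**Product status.** The synopsis states that "SGI-110 is considered as Investigational Medicinal Product (IMP" and says only that ipilimumab follows its approved dose and schedule. Section 5.1.1 states: "In this protocol, investigational products are SGI-110 and ipilimumab".

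**The concern.** A patient with a drug-related Grade 4 neutropenia or thrombocytopenia meets all three sets of rules, and they lead to different treatment. Section 1.5 names myelosuppression as one of the two main SGI-110 reactions. Section 1.3.5.1 expects recovery from it to be the likely determinant of the safe dose, and says little is known about cycles shorter than 28 days. This is therefore a foreseeable event in a trial of at most 19 patients.

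At stake are the outputs in 8.4.2 (extent of exposure, omissions and delays, adverse events leading to discontinuation) and how the efficacy estimates in 8.4.3 are read. Those estimates use all treated subjects, so they describe whatever mix of full and partial combination treatment was delivered. Tolerability, listed in 6.4.1 and defined in 5.3 by continuing for two consecutive cycles, is also exposed if continuing treatment means continuing both drugs.

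**Working it through.** The plan states no figure on this point, so there is nothing to reproduce. The check is a comparison of the rules, followed by a scale calculation.

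**1. The rules applied to one patient:** a drug-related Grade 4 cytopenia that is asymptomatic, uncomplicated and recovers within a week.

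| Source | SGI-110 | Ipilimumab |
|---|---|---|
| 5.3.2, Grade 4 bullet | not addressed | permanently stopped |
| 5.3.1, SGI-110 delay criteria | held, then same dose | held with all study drugs; a next dose is presupposed |
| 4.2.3, note (if the event leads to stopping one drug and is unequivocally due to it) | may stop | may continue, at discretion |

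Section 5.3.2 does not refer to the note, and no section says which rule governs.

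**2. Does the term drug-related separate the rules?** Not as written. Section 5.1 makes both products study drug, and both sets of delay criteria in 5.3.1 use drug-related to cover either agent. Where 5.3.1 means ipilimumab alone, as in the introduction to its ipilimumab delay criteria, it says so. The 5.3.2 bullet carries no such limit, but it does not state that it covers both drugs either.

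**3. Does the DLT route settle it?** No. Section 5.3 limits DLTs to Day 1 to Day 21 of Cycle 1, and counts Grade 4 neutropenia only if it lasts at least 5 days. Shorter neutropenias in Cycle 1, and cytopenias in Cycles 2 to 4, are outside that route. Inside it there is a second conflict: 4.2.3 makes DLT a mandatory stop for investigational product, while 5.3.1 allows SGI-110 to restart after a myelosuppressive DLT. SGI-110 is investigational in both the synopsis and 5.1.1, so this second conflict does not turn on how ipilimumab is classified.

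**4. Scale.** Section 1.3.5 gives Grade 3 or higher blood and lymphatic events: 272/357 = 76.2%, 41/47 = 87.2% and 46/68 = 67.6%. Grade 4 is not given separately. The proportion p of patients with a drug-related Grade 4 haematological event is therefore an assumption, taken over a wide range. Expected number among 19 = 19 × p; chance of at least one among n patients = 1 − (1 − p)^n.

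| Assumed p | Expected of 19 | At least 1 of 19 | At least 1 of 6 |
|---|---|---|---|
| 5% | 1.0 | 62% | 26% |
| 10% | 1.9 | 86% | 47% |
| 20% | 3.8 | 99% | 74% |
| 50% | 9.5 | over 99.9% | 98% |

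These count patients who would meet the conflicting rules. They do not count ipilimumab doses lost: infusions are at weeks 1, 4, 7 and 10, so an event after week 10 costs none.

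**The case against.** The best defence is that the sections address different drugs. Section 5.3.2 sits under an ipilimumab heading, and the delay rule sits under an SGI-110 heading and opens with events judged related to SGI-110. Redosing at the same level fits SGI-110, since ipilimumab has a single dose. On that reading SGI-110 resumes, ipilimumab stops, and nothing conflicts. It does not fit the rest of 5.3.1, which holds and releases all study drugs together regardless of attribution and times redosing by the next ipilimumab dose. That wording implies that ipilimumab continues, although it does not say so outright.

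The second defence is the note in 4.2.3. It addresses the case of a cytopenia from one drug removing the other, and it treats both drugs as investigational, so it works however ipilimumab is classified. Attribution may often be clear, since 1.3.5.1 says ipilimumab is not myelosuppressive. This has weight, but the note is discretionary and is not linked to 5.3.2, whose bullet is not discretionary. It adds a rule without ranking the rules.

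A third defence is that such events may be rare: 1.5 says no drug-related myelosuppression was reported at these doses and schedule in the AML/MDS study. The same paragraph names myelosuppression as a main reaction and points out that cycles here are 21 days. The low end of the assumed range allows for rarity.

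Uneven application would also be partly visible, because 8.4.2 tabulates omissions, reductions and delays and lists adverse events leading to discontinuation. Visibility after the fact does not give the site one rule to follow.

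**Conclusion.** The inconsistency stands on the text and does not depend on any rate. After a Grade 4 drug-related cytopenia, whether ipilimumab continues depends on the section followed. Whether SGI-110 may resume after a myelosuppressive DLT is a second, related conflict. Under an assumed 5% to 50% event rate, about 1 to 9.5 of 19 patients would meet the conflicting rules.

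Four stronger readings are not supported:

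- A reader might infer that several patients lose ipilimumab under 5.3.2 and none under 5.3.1. No Grade 4 rate is given, and ipilimumab can also stop for DLT, for a delay beyond 6 weeks, or on investigator judgement.
- A reader might take the rates in 1.3.5 as a guide to the Grade 4 rate. They are Grade 3 or higher for a whole organ class. The 68% comes from a carboplatin combination whose myelosuppression 1.3.5.2 describes as what carboplatin alone would produce.
- A reader might infer that the synopsis makes ipilimumab non-investigational. It names only SGI-110 as IMP and does not classify ipilimumab. The descriptions should match, but the synopsis does not say the opposite of 5.1.1.
- A reader might infer that the MTD is compromised. The MTD rule rests on Cycle 1 DLTs and is not directly affected. The efficacy endpoints are secondary and exploratory.

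**What to change.** Reconcile 4.2.3, both relevant parts of 5.3.1 (the opening paragraph and the SGI-110 delay criteria) and 5.3.2, so that one rule applies to each situation. The text should state:

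- whether Grade 4 haematological abnormalities fall under the permanent-discontinuation bullet in 5.3.2;
- whether drug-related in that bullet means related to ipilimumab or to either drug;
- whether the note in 4.2.3 overrides 5.3.2;
- how the mandatory stop for DLT in 4.2.3 fits with resuming SGI-110 after a myelosuppressive DLT in 5.3.1.

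Describe ipilimumab's product status in the same way in the synopsis and 5.1.1, so that the opening of 4.2.3 has one meaning. Which clinical rule applies is for the sponsor to decide; this point asks only that the sections agree. The cost is protocol wording, with no change to design, sample size or data collection.
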